**Fig. 1 Fig1:**
[figure not shown]
Study flow

### Randomisation and blinding

Participants will be randomised at the individual level using randomly permuted blocks. The randomisation sequence will be generated using a randomisation website [25]. Blocks of 15 allocations will be generated with a 1:1:1 ratio of study arm allocations to ensure a balance of five participants per study arm for each cohort. Each cohort of 15 participants will comprise patients recruited from a single GP practice site, or a single hub and spoke site grouping. Randomisation allocation will be concealed in consecutively numbered opaque sealed envelopes. As with all studies of this type it is not possible to blind participants, the recruiting nurse, or intervention facilitators to group allocation once the envelope has been opened. The data will be analysed by a researcher blinded to the allocation of the groups.

### Study interventions

#### Self-management intervention

Participants allocated to the SMI group and the SMI + RR group will attend group self-management sessions for 4 consecutive weeks, which will be held at a local GP surgery or community practice, in addition to their usual care. Each session will last approximately 2 hours, and will be facilitated by an SMI-trained practice or research nurse with experience of providing clinical care to patients with diabetes, paired with a health psychologist researcher or layperson. Ten participants will attend each SMI group (five SMI only, five SMI + RR). The facilitator will keep an attendance log. Intervention sessions will be audio recorded where participants provide permission, to investigate intervention fidelity.

All SMI facilitators will attend a 2-day self-management training course led by two experienced self-management practitioners and trainers. The training comprises teaching regarding theories of behaviour change and self-management. Facilitators will be taught how to use the SMI manual and will practice skills for managing groups. After training they will be supported to deliver the intervention through pre- and post-session briefing meetings each week within their facilitator pairings, and with the research team.

The SMI will be adapted from the UCL-DSMP [14]. See Additional file 2 for sample excerpts from the CoRDia SMI facilitator manual. For three of the four sessions the group will address specific target behaviours: medication adherence, healthy eating and physical activity respectively. For the fourth session, participants will be invited to identify additional target behaviours that they believe to be important in managing diabetes and/or CHD risk (e.g. foot care, smoking cessation). The following behaviour change techniques [26] will be delivered in each session:**Knowledge and information sharing**: Each session will include brief didactic teaching to ensure that all participants have a clear understanding of the importance of, and how to manage, their diabetes in relation to the target behaviour.**Problem solving**: Participants will be asked to brainstorm difficulties that they experience with \carrying out the target behaviour. Difficulties that several members of the group are experiencing, or would like to discuss, will be selected and strategies to overcome them elicited from the group. Strategies for several difficulties can be discussed, subject to the requirements of the group.**Action planning**: In the first session, the principles of goal setting and action planning will be didactically presented. At the end of each session participants will be invited to set a goal and develop a detailed written action plan for the following week, targeting the behaviour in question. The action plan includes information about the target behaviour, the frequency and intensity with which it will be carried out, and any plans they need to make to overcome anticipated difficulties. Participants will rate their confidence to carry out the behaviour on a scale of 1–10. Where participants wish to (e.g. if they do not have difficulties with taking medication), an alternative health behaviour can be targeted. The facilitator will provide support to write the action plan and then will model reporting their personal action plan to the group. The group will be invited to report their own.**Goal review and praise/reward**: For the second and subsequent sessions, goal review is carried out, where participants report back to the group about their goal attempt. Where a goal has been partially achieved or not achieved, strategies to overcome experienced problems will be briefly brainstormed by the group. Participants who have been successful or partially successful in achieving their goal will be praised by the facilitator and encouraged to recognise their success.

#### Risk results intervention

Participants allocated to the SMI + RR group will be asked to review and sign the consent form specific to the genetic test and provide a saliva sample for analysis using the Oragene DNA Self-collection Kit (DNA Genotek Inc., Ontario, Canada). Deoxyribonucleic acid (DNA) will be extracted according to the manufacturer’s instructions and analysed as described below. Participants will be invited to attend a one-on-one appointment with the researcher in the week prior to the first SMI group session, where a trained researcher will present the results of the risk report to each participant using a script to ensure consistency in delivery.

#### The risk report

Risk reports will be personalised to describe individual CHD risk, defined as risk of having a myocardial infarction (MI). There are three sections to the risk report, detailing (i) genetic lifetime CHD risk presented as a graph, with the patient’s personal risk relative to average risk, (ii) 10-year lifestyle CHD risk presented as a graph, reporting absolute and relative risk to the average person’s percentage risk. This is supported by text detailing the participant’s estimated lifestyle risk, the risk for the average person of their age, ethnic group and gender, and risk relative to the average person, expressed as a percentage. (iii) Combined genetic and lifestyle overall 10-year CHD risk presented in the same manner as lifestyle risk. The report will state that it is possible to reduce lifestyle risk by engaging in health behaviours e.g., eating more healthily and becoming more physically active, all of which are addressed in the SMI. Participants will be given their printed personalised risk report to keep for their own records; copies of individual’s risk reports will not be stored or made available to their care provider.

#### Genetic analysis and risk calculation

Genotypes for 19 CHD risk single nucleotide polymorphisms (SNPs) will be determined using the Randox Cardiac Risk Prediction Array (Randox Laboratories Ltd., Crumlin, UK). In the event of any discrepancies, genotypes will be confirmed by Sanger sequencing. The number of risk alleles for each SNP carried by an individual will be multiplied by its reported meta-analysis effect size for CHD, for method see [21] to give an individual’s genetic risk score. To put the genetic risk score into context, the individual genetic risk score will then be adjusted for the population average genetic risk score. The population average risk is calculated by multiplying the expected frequency of the three genotypes (based on the allele frequency determined in the source publications, see [21] for each SNP by the number of risk alleles corresponding to that genotype). These products are then summed for all the SNPs. The comparative average person is someone with type 2 diabetes of the same age, ethnicity and gender as the individual participant, with the average systolic blood pressure (BP) and lipid ratio determined using data from the University College Diabetes and Cardiovascular Study (UDACS) [27]; data presented in Additional file 3. An appropriate value for HbA1c has been set on advice from a group clinician. The 10-year lifestyle CHD risk will be estimated using the UKPDS risk engine v2.0 [28]. To give the combined 10-year CHD risk incorporating both lifestyle and genetic risk the population-adjusted genetic risk will be then added to the UKPDS risk.

### Usual care control group

Those randomised to usual care will be advised to continue to manage their diabetes as they would normally. Usual care will be documented across practices and community services involved in the study using a checklist informed by the General Medical Services QOF 2014/15 and NICE clinical guidelines for the management of type 2 diabetes (modified March 2014). The checklist will be developed in consultation with specialist primary care diabetes staff.

### Measures

#### Socio-demographic information

Age, ethnicity, marital status, and education and employment status will be collected at baseline. Participants will also be asked to self-report whether they have attended any health management programmes previously and to indicate if there is a known history of CHD in their immediate family.

### Primary outcomes

*HbA1c.* Change in blood glucose control as measured by glycated haemoglobin (HbA1c) will be recorded from patient’s medical records. HbA1c reflects average plasma glucose concentration over an 8–12-week period and will be collected at baseline and 6 and 12 months post-baseline.

*UKPDS risk.* Ten-year risk of CHD defined as fatal, and non-fatal, MI will also be calculated at baseline and 6 and 12 months post-baseline using the UKPDS risk engine (v2.0) [28]. UKPDS is a risk calculator specifically for people with type 2 diabetes. Percentage risk is calculated from participants’ age, years since diabetes diagnosis, presence of atrial fibrillation, reported smoking behaviour, sex, ethnicity, HbA1c, systolic BP, and total and HDL cholesterol.

### Secondary outcomes

#### Clinical

The following clinical measures will also be recorded from participant’s medical records at baseline, and 6 and 12 months post-baseline to be considered independently: (i) sitting systolic and diastolic BP, (ii) total cholesterol, (iii) HDL cholesterol, and (iv) BMI.

If available in patient records, the following additional measures will also be recorded: (i) smoking status, (ii) blood glucose fasting sample, (iii) low-density lipoprotein (LDL) cholesterol, (iv) triglycerides, (v) serum creatinine, (vi) estimated glomerular filtration rate (eGFR), (vii) urine albumin to creatinine ratio (urine ACR), (viii) foot risk assessment, and (ix) impotence.

The following self-reported behavioural, cognitive and psychological measures will be measured at baseline, immediately post-intervention (approximately 3 months post-baseline), and 6 months and 12 months post-baseline.

#### Behavioural

*The summaries of self-care activities measure* will assess diabetes self-management behaviours for diet, exercise, blood sugar testing, smoking and diabetes medications [29].

#### Cognitive predictors of health behaviours

The cognitive predictors of behaviour described in the HAPA will be assessed using measures adapted from those used for the Risk Appraisal Consequences in Korea Study [30]. Changes to wording have been made to increase clarity in English. Measures assess:*Perceived risk of developing heart disease*: The following three scales assess perceived risk in relation to six types of CHD: high cholesterol, heart attack, high blood pressure, stroke, angina, heart disease. Participants respond on a 7-point Likert scale for each item.*Absolute risk* assessing own perceived risk.*Absolute risk for average person with diabetes* assessing perceived risk of average person of same age, gender, ethnic group.*Comparative risk of developing CHD* assessing perceived risk in comparison with average person with diabetes.*Perceived severity of CHD*: assessed for each of the six types of CHD on a 7-point Likert scale for (i) average person, and (ii) self.*Intentions to engage in each of the five target behaviours*: healthy eating, physical activity, checking blood sugars (where prescribed), taking medication, stopping smoking. Participants respond on a 4-point Likert scale for each behaviour.*Planning with respect to five target behaviours*: five scales with up to 10 items assess plans for when, where, what to do, how often and plans needed to engage in each of the target health behaviours. Responses are given on a 4-point Likert scale.*Outcome expectancies towards each of target behaviours*: assessed on five scales comprising 6–12 items, relating to potential positive and negative outcomes of the target behaviour. Participants respond on a 4-point Likert scale.*Self-efficacy to perform each of the five target behaviours*:*Confidence to perform the behaviour regularly*: five items relating to target behaviours. Participants respond on a 10-point Likert scale.*Confidence to overcome barriers to target behaviour*: five scales relating to each target behaviour. Each scale has 10–13 items relating to problems that may be encountered.

Participants respond on a 10-point Likert scale.

### Psychological outcomes

*Depression and anxiety* will be assessed using the Hospital Anxiety and Depression Scale (HADS) [31] a 14-item questionnaire for use in patients with physical health problems. Total scores on each subscale are summed (score range = 0–21), with higher scores indicating greater levels of anxiety or depression. The HADS has demonstrated good reliability and validity among primary care patients [32].

*Health-related quality of life* will be assessed using the Short-Form Health Survey (version 2) (SF-12v2), which comprises two subscales: The Mental Component Score (MCS) and the Physical Component Score (PCS), reflecting mental and physical health-related quality of life respectively. Total scores range from 0–100 with higher scores indicating greater health status. Both subscales of the SF-12v2 have reported good reliability and validity [33].

### Response to risk results

For those in the SMI + RR group, participant responses to receiving personalised risk information will be assessed immediately post-intervention, and 6 and 12 months post-baseline.

*Recall and comprehension of risk results*: Questions will be developed for this study. Participants will be asked to recall from memory their absolute lifestyle and overall risk percentage, and to identify the description relative to the average person of their genetic risk result from a list of six statements. Comprehension of the genetic test result will further be assessed by asking participants to identify whether four descriptive statements about their result are true or false, e.g., ‘*Your genetic test result is based on the number of gene variants you have*’*.*

*Psychological impact of receiving a genetic and lifestyle risk result*: Will be assessed by adapting the Impact of Genetic Testing for Alzheimer’s disease (IGT-AD) scale [34] to make it appropriate to CHD risk. This measure comprises distress and positive experiences subscales; three questions will be eliminated from the distress subscale as they are not relevant to this study. Responses to this adapted 13-item measure will be recorded on a 5-point Likert scale, with higher scores indicating greater psychological distress; responses to the positive experiences subscale are reverse scored.

### Power calculation

A clinically important change in HbA1c level of 12.5 % (SD 15.5 %) was identified from a Health Technology Assessment of blood glucose monitoring devices [35] over a period of 18 months. This represents a reduction in HbA1c (%) from 8 to 7 or from 9 to 7.9. As the current study has a shorter follow-up, we base our sample size calculations on a conservative change that would be clinically achievable in this time frame: an HbA1c change of 6.25 % representing a reduction from an HbA1c (%) of 8 to 7.5 or from 9 to 8.44 (this represents a change from 63.9 mmol/ml to 59.9 mmol/ml; and 74.9 mmol/ml to 69.4 mmol/ml).

The expected 6.25 % change in HbA1c (SD = 15 %) represents an effect size of d = 0.40, a small to moderate effect size (d = 0.2 – small, 0.5 – medium and 0.8 – large effect); equivalent to effect size f = 0.2 in G*Power [36] calculated for repeated measures, between-subjects analysis of variance (ANOVA) analyses. Based on the current design (three groups, four measurement points), alpha = 0.05, power = 80 %, f = 0.20 and a correlation between measurement points of 0.70, G*Power indicates a total sample size of 192. With an expected attrition rate of 20 %, a sample size of 240 (80 per study arm) will be sought.

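### The sample size uses an SD printed for a change in HbA1c where the routine needs the SD at one visit, so the stated 80 % power does not follow from the inputs as printed

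*Protocol article*

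**What the plan says.** All of this is in the protocol article, section Power calculation.

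- The starting point is an external assessment covering 18 months: "A clinically important change in HbA1c level of 12.5 % (SD 15.5 %) was identified". The section illustrates this as a fall in HbA1c from 8 to 7.
- Because follow-up here is shorter, the effect is halved: "The expected 6.25 % change in HbA1c (SD = 15 %) represents an effect size of d = 0.40". The illustration is again a fall over time, from 8 to 7.5.
- That d is declared "equivalent to effect size f = 0.2 in G*Power [36] calculated for repeated measures, between-subjects analysis of variance (ANOVA) analyses".
- The remaining inputs are "Based on the current design (three groups, four measurement points"), then "alpha = 0.05, power = 80 %, f = 0.20" and "a correlation between measurement points of 0.70, G*Power indicates a total sample size of 192".
- Finally, "With an expected attrition rate of 20 %, a sample size of 240 (80 per study arm) will be sought".

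The section does not say whether the 15 or 15.5 % is the SD of within-person change or the between-patient SD of HbA1c expressed as a percentage. It gives no origin for the 0.70.

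**The concern.** Both times an SD appears, it is attached to a change in HbA1c. The natural reading is the SD of that change. The repeated-measures between-subjects routine works on another scale: its f is the spread of group means divided by the SD of the outcome at one measurement point, and it uses the correlation to work out the variance of each patient's mean over the visits.

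The two SDs are equal only when the baseline-to-follow-up correlation is 0.5. At the protocol's 0.70 the SD of change is smaller than the SD of the level. Using the smaller SD in place of the larger overstates d and therefore power.

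HbA1c is one of the two primary outcomes, and the target of 240 rests wholly on this paragraph. A null result would be read against a claimed 80 % power that the printed inputs do not support.

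**Working it through.** **Inputs (Power calculation).** Effect 6.25 %; SD 15 % (source 15.5 %); d = 0.40; f = 0.20; k = 3 groups; m = 4 points; rho = 0.70; alpha = 0.05; N = 192. Equal allocation is from Randomisation and blinding ("Blocks of 15 allocations will be generated with a 1:1:1 ratio of study arm allocations"). The step f = d/2 and the four points are kept as the protocol has them, so that only the SD changes.

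**Step 1: reproduce the plan.** Between-subjects F test with noncentrality lambda = f² × N × m / (1 + (m − 1) × rho), on k − 1 = 2 and N − k = 189 degrees of freedom.

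lambda = 0.04 × 192 × 4 / (1 + 3 × 0.70) = 30.72 / 3.1 = 9.91, so power = 80.5 %. The smallest total divisible by three that reaches 80 % is 192, and 192 / 0.80 = 240. Both printed figures reproduce.

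**Step 2: check d.** 6.25 / 15 = 0.417; 6.25 / 15.5 = 0.403. The printed d = 0.40 matches 15.5 %, not the 15 % beside it.

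**Step 3: convert a change SD to a level SD.** With equal variances, SD of change = SD of level × sqrt(2 × (1 − rho)). At 0.70 the factor is sqrt(0.6) = 0.775. The level SD is then 15 / 0.775 = 19.4 % or 15.5 / 0.775 = 20.0 %.

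**Step 4: rerun the same routine at N = 192.**

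| Starting d | Level d | f | lambda | Power | Completers for 80 % (recruited) |
|---|---|---|---|---|---|
| 0.40 | 0.310 | 0.155 | 5.95 | 57.3 % | 315 (394) |
| 6.25/15.5 = 0.403 | 0.312 | 0.156 | 6.04 | 58.0 % | 312 (390) |
| 6.25/15 = 0.417 | 0.323 | 0.161 | 6.45 | 61.0 % | 291 (364) |

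**Step 5: vary the conversion correlation.** The 0.70 is stated for this trial's visits, not for the external source. The routine's own rho stays at 0.70.

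| Conversion correlation | Factor | Power from d = 0.40 | Power from d = 0.417 |
|---|---|---|---|
| 0.5 | 1.000 | 81 % | 84 % |
| 0.6 | 0.894 | 71 % | 74 % |
| 0.7 | 0.775 | 57 % | 61 % |
| 0.8 | 0.632 | 41 % | 44 % |

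**Step 6: analyse change directly.** If the SD is of change, no conversion is needed for a one-way three-arm ANOVA of change, and lambda = f² × N. For f = 0.20, lambda = 0.04 × 192 = 7.68 and power is 69 %. For f = 0.417/2 = 0.208, lambda = 8.33 and power is 73 %. Reaching 80 % would need 246 or 228 completers.

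**Step 7: adjust for baseline.** With level SD 19.4 % and rho 0.70, the residual SD at one follow-up is 19.4 × sqrt(1 − 0.49) = 13.8 %. Then f = 6.25 / 13.8 / 2 = 0.226, lambda is about 9.8 and power is about 80 %.

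**The case against.** The strongest reply is that the text does not prove 15 % to be a within-person change SD. A between-patient SD expressed as a percentage is also open: 15 % of an HbA1c of 8 is 1.2 percentage points. Only the cited source could settle it, and it is not at hand. On that reading d = 0.40 is already on the scale the routine needs, and nothing is lost. This stands, so the loss of power is conditional.

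Three stronger readings are tempting, and the document does not support them.

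- *The correlation is counted twice.* A reader might infer this from a change SD combined with a correlation of 0.70. In this routine, however, a higher correlation lowers power: at f = 0.20 and N = 192 it is 89 % at 0.5, 80.5 % at 0.7 and 77 % at 0.8. The fault is one of scale, with a gain from averaging four points added on top.
- *Power is about 57-61 %.* That figure also needs 0.70 to hold for an external 18-month source, which nothing in the document says. The conversion formula is for absolute differences with equal variances, so applying it to a percentage change is an approximation.
- *57-61 % is the power of the planned analysis.* The routine tests group means averaged over all visits, baseline included. Main analyses plans a 3 x 3 mixed ANCOVA, or multi-level modelling in its place. Step 7 shows that a baseline-adjusted model can recover about 80 % under the same assumptions.

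It can also be said that the 15 versus 15.5 discrepancy is small and that d = 0.40 is the cautious side of it. That is right, and the discrepancy is only a minor point here.

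The objection does not remove the mismatch itself. On the printed wording, the stated calculation does not deliver its 80 %, and neither does a direct analysis of change.

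**Conclusion.** The point holds in conditional form and should be corrected. The arithmetic of the printed calculation is sound, but its SD is described on one scale and used on another.

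- If the SD is of change, as printed, 80 % at N = 192 does not follow. The stated routine gives about 57-61 % with conversion at 0.70, and the result is sensitive to that choice (no loss at 0.5, 41-44 % at 0.8). Direct analysis of change gives about 69-73 %.
- If the SD is of the HbA1c level, the 80 % stands on this point, and the words tying the SD to a change are the error.

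All figures assume f = d/2. Those from the stated routine also assume four measurement points, as the protocol does. As printed, a reader cannot tell which case applies, so this is more than a matter of style.

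**What to change.** In Power calculation:

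1. State whether the SD is of percentage change or of the HbA1c level, and use one value throughout. 15.5 % is the one that matches d = 0.40.
2. If it is a change SD, either convert it to the level scale, naming the correlation used and showing a range, or compute power directly for the between-arm difference in change or for a baseline-adjusted model. Use the three HbA1c visits listed under Primary outcomes (baseline, 6 and 12 months).
3. If it is a level SD, reword the sentence so that the SD is no longer attached to a change.
4. Keep the target of 240 and restate the power obtained.

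The cost is one rewritten paragraph and a recalculation, with no additional patients. The only downside is that the stated power may be less favourable.

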## Methods/Design

A three-arm randomised controlled trial (RCT). Eligible participants will be randomly allocated to either a group self-management intervention (SMI), SMI plus risk results (SMI + RR), or standard usual care. See Additional file 1 for the complete SPIRIT checklist.

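### The power calculation turns d = 0.40 into f = 0.20 by the two-group rule and enters it in a three-group routine; for three arms f is 0.163 to 0.189, and the routine gives 62–75 % power at N = 192 (66–79 % with unrounded d)

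*Protocol article*

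**What the plan says.** The Power calculation section of the protocol article gives a single effect: "The expected 6.25 % change in HbA1c (SD = 15 %) represents an effect size of d = 0.40". It then describes this as "equivalent to effect size f = 0.2 in G*Power [36] calculated for repeated measures", for "between-subjects analysis of variance (ANOVA) analyses". The remaining inputs are "alpha = 0.05, power = 80 %, f = 0.20 and a correlation between measurement points of 0.70", entered for three groups and four measurement points ("Based on the current design (three groups, four measurement points"). The result is that "G*Power indicates a total sample size of 192", raised to 240 (80 per arm) for 20 % attrition. Methods/Design confirms three arms ("A three-arm randomised controlled trial (RCT"), and Randomisation and blinding fixes 1:1:1 allocation.

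The section does not say between which arms the 6.25 % applies, nor where the third arm is expected to lie.

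**The concern.** In an analysis of variance, f is the standard deviation of the group means divided by the within-group standard deviation. With two equal groups that differ by d, this is d/2. With three groups it depends on where the third mean lies, and for a given largest difference it is always below d/2. An f derived for two groups has therefore been entered in a test of three, which overstates the noncentrality.

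This paragraph is the only justification given for the sample size. A reader of a null overall result would take it that the trial had been sized with 80 % power against a 6.25 % difference. The printed inputs do not support that statement.

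**Working it through.** **Inputs, all from the Power calculation section unless noted.** alpha = 0.05; power 80 %; d = 0.40 (from 6.25 % and SD 15 %); f = 0.20; k = 3 groups; m = 4 points; rho = 0.70; N = 192; attrition 20 %; equal allocation (Randomisation and blinding).

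**Step 1: reproduce the stated N.** The between-factors repeated-measures routine uses a noncentral F with df = k − 1 and N − k, and lambda = N·f²·m / (1 + (m − 1)·rho).

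- The denominator is 1 + 3 × 0.70 = 3.1.
- At N = 192 and f = 0.20, lambda = 192 × 0.04 × 4 / 3.1 = 9.91, which gives 80.5 % power.
- N = 189, the next smaller multiple of 3, gives 79.8 %.
- 192 / 0.80 = 240.

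The stated 192 and 240 therefore reproduce. With k = 2 the routine would give 156 and with m = 3 it would give 198, so the run did use three groups and four points.

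**Step 2: f for three equal arms with largest difference d.**

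- Middle arm halfway (0, d/2, d): f = d/√6, the smallest possible value.
- Two arms tied (0, 0, d or 0, d, d): f = d·√2/3, the largest possible value.

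At d = 0.40 these are 0.163 and 0.189, so no pattern reaches 0.20. At the unrounded d = 6.25/15 = 0.417 they are 0.170 and 0.196.

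**Step 3: power at N = 192, other inputs as stated (m = 4).**

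| d | Pattern | f | Power |
|---|---|---|---|
| 0.40 | middle arm halfway | 0.163 | 62.1 % |
| 0.40 | third arm at 0.1 or 0.3 | 0.170 | 65.8 % |
| 0.40 | two arms tied | 0.189 | 75.4 % |
| 0.417 | middle arm halfway | 0.170 | 65.9 % |
| 0.417 | two arms tied | 0.196 | 79.0 % |

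**Step 4: the same with three points.** Primary outcomes lists HbA1c and UKPDS risk at baseline, 6 and 12 months, so m = 3 and the denominator is 1 + 2 × 0.70 = 2.4. Power at N = 192 is 60.6–74.0 % at d = 0.40 and 64.4–77.6 % at d = 0.417. At f = 0.20 it is 79.2 %.

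**Step 5: what f = 0.20 means for three arms.** The largest difference must be 0.20 × 3/√2 = 0.424 SD (two arms tied) to 0.20 × √6 = 0.490 SD (middle arm halfway). At SD 15 % that is 6.4 % to 7.3 % relative HbA1c, against the stated 6.25 %.

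**The case against.** **Rounding.** The primary inputs are 6.25 % and SD 15 %, not 0.40. From these, with two arms tied, f is 0.196, which rounds to the 0.20 entered, and power is 79.0 %. This stands: in that one case the error is little more than rounding. It does not rescue the text, which prints d = 0.40 and derives f from it; with the middle arm halfway, the unrounded d still gives only 65.9 %.

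**The low end is the least favourable pattern.** This also stands. An expected ordering of usual care, SMI and SMI + RR does not place the middle arm at the midpoint. The Background reports that self-management interventions improve glycaemic control and that evidence for risk information alone is limited, so a pattern close to two tied arms is just as compatible with the text. The range should be shown, not its lower end alone.

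**0.40 might be the step between neighbouring arms.** Means of 0, 0.40 and 0.80 would give f = 0.327 and power above 99 %. Nothing in the section says this. It would make the full range 12.5 %, the 18-month figure that the section sets aside for its shorter follow-up, and it would not produce the f = 0.20 that was entered.

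**The sizing routine is not the planned analysis.** The Main analyses section plans a 3 x 3 mixed ANCOVA. The routine assumes a full difference at every point, baseline included. Assume instead compound symmetry with rho = 0.70, no baseline difference, and d = 0.40 at both 6 and 12 months. At N = 192 a group-by-time test then has about 77 % (halfway) to 89 % (tied) power, while a main effect averaged over all three points has about 30–39 %. This stands and limits what can be concluded.

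**Conclusion.** The conversion is wrong as printed. On the condition that 0.40 SD is the largest difference among three equal arms, which is the natural reading of a section that gives only one effect, the stated routine at N = 192 yields 62–75 % power instead of 80 %, or 66–79 % with d unrounded. The gap is negligible only if two arms tie and the unrounded d is used.

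A reader might infer that the trial itself has only 62–75 % power, or that 240 is too few. The documents do not support either. The figures correct one input of a between-subjects calculation that differs from the planned analysis in its measurement points and in its test, and power under the planned analysis could be higher or lower depending on which effect is tested. Nor does the article fix the pattern of means that would single out the lower figure. The point is a misstated justification that should be corrected. It alters no arm, endpoint or analysis, and it does not bias the effect estimates.

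**What to change.** Keep 240. In the Power calculation section, delete the statement that d = 0.40 is equivalent to f = 0.2, name the assumed pattern of the three arm means, and restate the power for that pattern with the three points at which HbA1c is measured. At N = 192 this is about 61 % (middle arm halfway) to 74 % (two arms tied) for d = 0.40, or 64 % to 78 % for d = 0.417.

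Alternatively, keep f = 0.20 and state that in three arms it corresponds to a largest difference of 0.42–0.49 SD (6.4–7.3 % HbA1c at SD 15 %), for which the routine at N = 192 gives about 80 % power with four points and 79 % with three.

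Either way, add that these figures refer to the between-subjects routine used for sizing and not to the 3 x 3 mixed ANCOVA. The cost is one reworded paragraph and a less favourable stated power or detectable difference; no further patients and no change of analysis are needed.
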